## Abstract

**Background:**

Sufferers from bulimia nervosa (BN) and binge eating disorder (BED) underestimate the severity risk of their illness and, therefore, postpone seeking professional help for years. Moreover, less than one in five actually seek professional help and only 50% respond to current treatments, such as cognitive behavioral therapy (CBT). The impetus for the present trial is to explore a novel combination treatment approach adapted from physical exercise- and dietary therapy (PED-t). The therapeutic underpinnings of these separate treatment components are well-known, but their combination to treat BN and BED have never been previously tested. The purpose of this paper is to provide the rationale for this new treatment approach and to outline the specific methods and procedures.

**Methods:**

The PED-t trial uses a prospective randomized controlled design. It allocates women between 18 and 40 years (BMI range 17.5–35.0) to groups consisting of 5–8 members who receive either CBT or PED-t for 16 weeks. Excess participants are allocated to a waiting list control group condition. All participants are assessed at baseline, post-treatment, 6, 12 and 24 months’ post-follow-up, respectively, and monitored for changes in biological, psychological and therapy process variables. The primary outcome relates to the ED symptom severity, while secondary outcomes relates to treatment effects on physical health, treatment satisfaction, therapeutic alliance, and cost-effectiveness. We aim to disseminate the results in high-impact journals, preferable open access, and at international conferences.

**Discussion:**

We expect that the new treatment will perform equal to CBT in terms of behavioral and psychological symptoms, but better in terms of reducing somatic symptoms and complications. We also expect that the new treatment will improve physical fitness and thereby, quality of life. Hence, the new treatment will add to the portfolio of evidence-based therapies and thereby provide a good treatment alternative for females with BN and BED.

**Trial registration:**

Prospectively registered in REC the 16th of December 2013 with the identifier number 2013/1871, and in Clinical Trials the 17th of February 2014 with the identifier number NCT02079935.

## Background

The present paper reports on an ongoing, new treatment for bulimia nervosa (BN) and binge eating disorders (BED). Binge eating disrupts normal eating patterns and introduces vicious circles of fasting and binging that causes a chaotic energy intake. Also, binge eating causes an energy surplus, which those with BN compensate for by purging, *eg.* vomiting, using laxatives, diuretics, or enemas, misusing medications or exercising in an extreme or rigid manner, all which can change body metabolism. It is noteworthy that such changes may also be the result of physical inactivity, which is frequently observed particularly among sufferers from BED.

Binge eating and compensatory behaviors can raise the medical severity of BN and BED by means of hypokalemia, that may elicit inter-current infections as well as cardiac complications, diseases or arrest, or it may affect glucose, insulin and lipid levels that increases the risk of type-2 diabetes [1–5]. A combination of rigid exercising and eating may over time inflict chronic low energy availability and raise the risk for low bone mineral density, and ultimately osteoporosis [6, 7]. The non-medical severity comprises personal and familial burdens. A slightly raised standardized mortality rate is due to both medical and non-medical burdens [8–10]. According to a recent systematic review, the societal health care costs range from €888–18,283 for BN and €1762–2902 for BED [8–10].

Most sufferers do not acknowledge the clinical severity and the medical and non-medical risks of eating disorders (ED), as 80–94% of people with BN and BED never seek professional help or delay it 4–5 years [11–15]. Effective treatment of BN and BED is considerably hampered by this incongruence, which may be circumvented by offering treatment options outside the contexts of traditional health services or improving access to such options. Among those who do enter treatment, a protracted course of illness is typically seen among every third patient [16]. Important reasons are early drop-out due to a failure to engage patients into treatment and lack of rapid symptom changes or symptom coping, thereby lowering patients’ motivation and self-efficacy [17].

In most treatment guidelines, cognitive-behavioral therapy (CBT) is regarded as the treatment-of-choice for BN [18]. Clinical targets in CBT include weakening the strength of core beliefs about low self-worth and compensatory beliefs about the need to control food intake, body weight and shape. Use of stimulus-control procedures to reduce the frequency of disordered eating, *ie.* bingeing and/or purging [19] is also central. Studies, systematic reviews and meta-analyses show promising effects of CBT for BED, and intermediate effects for BN, but the methodological quality of studies is low to moderate [20–22] even when often observed comorbid conditions are incorporated in the treatment [23–25]. New treatment approaches are called for because up to 50% of patients do not respond to CBT, even when the therapy is especially designed for ED [26].

Guided physical exercise (PE) may facilitate regulation of negative emotions [27], yet guided PE is rarely used in clinics [28] due to a fear of reinforcing the excessive exercise used to compensate for bingeing. A previous randomized controlled trial has shown that guided PE is as effective as CBT in alleviating BN symptoms [29]. The present study aims to replicate and expand on these findings.

Dietary therapy (DT) and counseling alone to correct the chaotic eating pattern has unclear empirical support [5, 30], but one review indicate some support to a possible *additive* effects of DT with CBT [31]. The present trial is the first one to examine the additive effects of DT and PE (PED-t) compared to CBT alone, and using a group therapy format.

Therapeutic alliance is an important moderator (or even mediator) of treatment effects in general; however, for EDs its impact is less understood [18, 32, 33]. High treatment expectations and installment of hope seems to predict treatment alliance in anorexia nervosa, but the relationship is uncertain for BN and BED [34]. Recent literature reviews have shown inconsistent findings across ED diagnoses, treatments, patient age groups and time (*eg*. early, mid or late) of assessment [31, 35, 36]. We hence included measures of alliance and group climate after every CBT and PED-t session to study the temporal order between these factors and response in both treatment arms [31].

### Hypotheses and predictions

This trial will test six hypotheses:

1) Comparison of treatment arms: a) PED-t and CBT have comparable effects in terms of less symptoms of eating pathology, b) both perform better than a wait-list control group in reducing binge eating and/or purging, and c) both improve dietary intake.

2) Compared with CBT, the PED-t intervention produces a more rapid treatment response.

3) By improving physical strength and endurance, body composition, bone mass, and the nutritional and hormonal status, PED-t will surpass CBT in reducing the number and severity of medical complications.

4) Positive early changes in therapeutic alliance scores and group cohesiveness partly mediate effects of PED-t and CBT.

5) PED-t surpasses CBT in terms of a lower dropout rate and higher patient satisfaction with treatment.

6) The direct treatment costs are comparable for PED-t and CBT, but the indirect costs of PED-t are expected to be lower.

We predict that the PED-t combination will serve as an effective treatment method for BN and BED because the preoccupations of exercise and diets are transformed away from being ED-symptoms and toward functional coping and self-regulative activities. We also predict that the treatment effect of PED-t will be rapid and strong, defined according to a systematic review and meta-analysis [37], and the best empirically derived predictors of sustained remission at 6 and 12 months follow-up [38, 39] *ie*. as a 25% reduction in depression scores and ≤3 binge eating episodes a week during the first four weeks of treatment. Given that our novel treatment (PED-t) targets clinical features that occupy the sufferers’ minds, we expect a high level of treatment engagement, motivation and compliance. Such accomplishments may facilitate a stronger therapeutic alliance [40].

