### Statistical power and analyses

Analysis of covariance (ANCOVA) is used to raise statistical power. The effect size of the covariates is set to *R*
^*2*^ = 25%, alpha = .05 and 1-beta = .80. The CBT treatment effect for EDs using the Eating Disorder Examination Questionnaire is about *d* = 1.30 [45]. A small change (*d* = 0.30) in the wait-list condition requires 14 subjects in each group (total *N* = 28), but since the difference between the PED-t and CBT treatment conditions is of primary interest a non-inferiority margin of *d* = 0.45 is considered as clinically relevant [46]. This requires a sample size of 62 + 62 subjects, increasing to 72 + 72 when adjusting for the group therapy factor (intra-class correlation = .05, design factor 1.16). The longitudinal data will be analyzed using multilevel regression models to accommodate for dependency in the repeated data within subjects and within groups. The maximum likelihood procedure uses all information available, thus, handling dropout well. Multiple imputation will be used to impute missing values. Follow-up data is analyzed with mixed model regression to estimate correct between-group treatment effects adjusted for within-group variance components related to patients and groups. Moderator variables will be included to analyze whether any treatment effects are modified by variables as motivation, therapist alliance or group cohesiveness. If treatment arms do not differ in outcome, combined latent class growth curve modeling will be conducted to analyze reasons for individual differences at startup and in the rate of change across time.

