In recent years, dissemination has been highly at focus with respect to CBT [88], showing that CBT can be delivered by health professionals other than heavily trained and payed psychologists and psychiatrists. An affordable and tolerable new program with an equal or better effect than CBT would represent major societal benefits in the sense that the PED-t can be delivered by new groups of professionals, *eg*. exercise therapists and registered dietitians, hence a possibility of reaching out to new segments of those sufferers who are reluctant to seek help through the health care services.

However, a concern can be raised about treatment effectiveness, *ie*. how well the PED-t might perform in clinical settings. Two deviations from such settings should be mentioned, i.e. the failure to offer booster sessions to consolidate changes during treatment, and to exclude severe comorbid conditions frequently found among patients with BN and BED [89–93], notably anxiety, depression, personality disorders, and active substance abuse. Regrettably, on the other hand, a long waiting time before starting treatment would actually mirror real life clinical settings. The impact of such waiting time on drop-out rates from treatment does, however not seem relevant here as such impact is relevant mostly for patients with severe comorbid conditions [94].

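### Hypothesis 1a and the abstract read as a two-sided claim of similarity, but the sample size and its 80% power are for one-directional non-inferiority

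*Protocol article*

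**What the plan says.** Four places in the protocol article bear on this.

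- Hypotheses and predictions, hypothesis 1a: "PED-t and CBT have comparable effects in terms of less symptoms of eating pathology".
- Abstract, discussion paragraph: "We expect that the new treatment will perform equal to CBT in terms of behavioral and psychological symptoms". The same sentence then expects PED-t to do better on somatic outcomes.
- Statistical power and analyses: the PED-t versus CBT difference is named as the primary interest, and "a non-inferiority margin of *d* = 0.45 is considered as clinically relevant". The inputs are "alpha = .05 and 1-beta = .80", with ANCOVA covariates taken to explain 25% of the variance (R²). The result: "This requires a sample size of 62 + 62 subjects, increasing to 72 + 72 when adjusting for the group therapy factor". That last step uses an ICC of .05 and a design factor of 1.16.
- Discussion, on dissemination: "An affordable and tolerable new program with an equal or better effect than CBT would represent major societal benefits".

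The sidedness of alpha is not given. No equivalence test, ± margin or pair of confidence limits is mentioned.

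**The concern.** A non-inferiority margin has one direction. It rules out that PED-t is worse than CBT by 0.45 or more, and it is also met when PED-t is clearly better. A statement that two treatments are comparable or equal excludes a relevant difference either way, so both confidence limits must lie inside ±0.45. The first two places above read as the second kind of claim, while the sizing is for the first kind.

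The article's own usage supports the two-sided reading. The other hypotheses use directional words where a direction is meant: better than wait-list, more rapid, surpassing CBT, lower dropout. Hypothesis 6 sets comparable direct costs against lower indirect costs. The abstract sets equal on one group of outcomes against better on another. The statistical section also makes a later latent class analysis depend on the arms not differing, a condition without direction that a non-inferiority result cannot establish.

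At stake is what may be concluded on the primary comparison. A successful non-inferiority test reported as comparable effects would claim more than was shown. If two-sided similarity were tested, the printed 80% would not be its power.

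**Working it through.** **Inputs.** From Statistical power and analyses: margin 0.45 in SD units, alpha .05, power .80, R² = .25, 62 per arm before clustering, ICC .05, design factor 1.16. From Methods and design: groups of 5–8. Assumption: true difference 0, which is not printed but fits the wording of hypothesis 1a.

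**Step 1: reproduce the printed size as non-inferiority.**

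n per arm = 2(1 − R²)[(z for 1 − α + z for .80)/0.45]²

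- One-sided .05, no R²: 2 × [(1.645 + 0.842)/0.45]² = 61.06, so 62. The t version also gives 62.
- One-sided .025, R² = .25: 1.5 × [(1.960 + 0.842)/0.45]² = 58.14, so 59; t version 60.
- One-sided .05, R² = .25: 45.8, so 46; t version 47.
- One-sided .025, no R²: 77.5, so 78; t version 79.

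Only the first two give about 62, and the first gives it exactly. The wait-list calculation points the same way: d = 1.30 − 0.30 = 1.00 at one-sided .05 without R² gives the printed 14 per group (t version), while the other three combinations give 11, 13 and 17. Clustering: 62 × 1.16 = 71.9, so 72. The printed size is therefore a non-inferiority size.

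**Step 2: power at 62 effective per arm for each criterion.** With SE = √(1 − R²) × √(2/62), non-inferiority power is Φ(0.45/SE − z). Power of two one-sided tests within ±0.45 at true difference 0 is 2Φ(0.45/SE − z) − 1.

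- Without R²: SE = 0.1796 and 0.45/SE = 2.506. At .05: Φ(0.861) = .805, and 2 × .805 − 1 ≈ .611.
- With R² = .25: SE = 0.1555 and 0.45/SE = 2.893. At .025: Φ(0.933) = .825, giving .649. At .05: Φ(1.248) = .894, giving .788.

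| Alpha per side | R² | n per arm, non-inferiority (normal / t) | Non-inferiority power at 62 | Two-sided power at 62 (normal / t) |
|---|---|---|---|---|
| .05 | 0 | 62 / 62 | 80.5% | 61.1% / 60.4% |
| .025 | .25 | 59 / 60 | 82.5% | 64.9% / 63.9% |
| .05 | .25 | 46 / 47 | 89.4% | 78.8% / 78.4% |
| .025 | 0 | 78 / 79 | 70.7% | 41.5% / 40.2% |

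At true difference 0, two-sided power is twice the non-inferiority power minus 1, so 80% becomes about 60%. Any other true difference lowers it.

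**Step 3: size for 80% two-sided power.** n = 2(1 − R²)[(z for 1 − α + z for .90)/0.45]². The first row needs 85 effective per arm (86 with t), or 99–100 after × 1.16. The second needs 78 (79 with t), or 91–92. The third needs 64, or 75.

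**Step 4: dependence on the design factor.** With 1 + (m − 1) × .05, groups of 5 give 1.20 and groups of 8 give 1.35, against the printed 1.16. Then 72 per arm is 60 to 53 effective. Two-sided power (normal) becomes 58.8% to 50.3% on the first row, 62.4% to 53.1% on the second and 77.0% to 70.1% on the third.

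**The case against.** The strongest reply is that this is a non-inferiority trial with informally worded hypotheses. The statistical section makes the primary comparison operational through a non-inferiority margin, and the Discussion counts an equal or better effect as success, which is one-directional. The word equal appears in the abstract, not in hypothesis 1a, and there it is an expectation. Expecting no difference is the usual assumption behind non-inferiority sizing. This stands: equivalence is one reading of hypothesis 1a, not a stated test, and if non-inferiority is intended the printed 80% belongs to the intended criterion.

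A reader might infer more: that the trial is underpowered at about 60–64% and that truly equal treatments would fail in about four trials in ten. The document does not support that as a flat statement. It depends on an equivalence test that is not specified and on choices of alpha and R² that are not printed. The 60% figure leaves out the stated R². The 64% figure needs .025 per side, which is not stated. With .05 per side and the stated R² it is 78–79%. That combination does not explain the printed 62, but the power of the test depends on the analysis that is run, not on how 62 was reached.

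A condensed article may also leave the formal decision rule to the analysis plan. That excuses a missing rule. It does not excuse printed wording that differs from the printed sizing.

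**Conclusion.** The mismatch holds. Hypothesis 1a and the abstract sentence read as two-sided similarity; the sample size, and the Discussion's equal-or-better aim, fit non-inferiority. The 80% power covers only the conclusion that PED-t is not worse than CBT by d = 0.45 or more.

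The size of the gap is conditional. Taking 62 effective per arm, margins of ±0.45 and a true difference of 0, two-sided power is about 60–65% under the two readings that give about 62, and about 78–79% with .05 per side and R² = .25. All are lower if the design factor exceeds 1.16. No single one of these figures should be printed as the trial's corrected power. The defect lies in the claim and its wording, not in a demonstrated shortfall of enrolment.

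**What to change.** Reword hypothesis 1a and the abstract sentence to the claim that was sized: PED-t is non-inferior to CBT on the EDE-q, margin d = 0.45, judged by the confidence limit on the side unfavourable to PED-t. State whether alpha is one- or two-sided and whether R² = .25 was applied in reaching 62. The cost is a narrower claim; enrolment and data collection do not change.

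If the comparable wording is kept, require both confidence limits to lie within ±0.45 and restate the power from the final alpha, R² and design factor. Step 3 gives the price of 80% power at the 1.16 factor: about 91–100 per arm under the two readings that match 62, or 75 with .05 per side and R² = .25, against the planned 72.

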## Methods and design

This randomized controlled trial includes three groups: participants are randomized to either the CBT or the PED-t treatment group, while participants having to wait represent the control group condition. After 16–20 weeks, these are randomized to either treatment arm. The treatments are delivered to groups consisting of 5–8 participants. It includes 20 therapy sessions stretching across 16 weeks. All outcome variables are measured five times: pre, post, 6, 12 and 24 months (Fig. 1). Mediator/moderator data (*ie*. therapy process variables) are collected after each treatment session, which yields excellent statistical power for conducting growth curve modeling, nuanced mediation or moderation analyses.

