### Randomization

The participants complete the baseline measures before randomization. We use block randomization of size eight (https://www.randomizer.org/) to ensure equal sized treatment arms. A project-independent fellow worker allocated eligible participants to either treatment arm according to a concealed randomization list. Researchers and test personnel in the study are blind with regard to group allocation, but due to the nature of the two treatment procedures, therapists and participants are obviously not blinded to the treatment allocation. The participants are informed about their group allocation after completing the baseline measures.

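### Hypothesis 1b is not a randomised comparison: the wait-list is filled by overflow, although the trial is described as randomised with three groups

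*Protocol article*

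**What the plan says.** The Methods and design section of the Protocol article opens with the design label: "This randomized controlled trial includes three groups". The same sentence goes on to say that "participants are randomized to either the CBT or the PED-t treatment group, while participants having to wait represent the control group condition". The Abstract (Methods) states how the control group is filled: "Excess participants are allocated to a waiting list control group condition". On what happens to these women afterwards, Methods and design says: "After 16–20 weeks, these are randomized to either treatment arm".

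The Randomization section describes one list: "A project-independent fellow worker allocated eligible participants to either treatment arm according to a concealed randomization list". Its blocks of eight are there "to ensure equal sized treatment arms". No wait-list allocation or ratio is mentioned.

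Under Hypotheses and predictions, hypothesis 1b is that "both perform better than a wait-list control group in reducing binge eating and/or purging". Statistical power and analyses gives this contrast its own sample size, 14 per group (28 in total), from a CBT effect of d = 1.30 and a wait-list change of d = 0.30, with "alpha = .05 and 1-beta = .80". The same section says that PED-t versus CBT is of primary interest and sizes the trial on it at 72 + 72.

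**The concern.** If chance decides only between CBT and PED-t, and surplus over available places decides who waits, then women on the wait-list may differ from women treated at once for reasons unrelated to treatment. Time of enrolment is the obvious one, since treatment groups run through 2014–2016. A difference in 1b could then partly reflect who waited and when.

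Hypothesis 1b is the only comparison with an untreated group, and it is available only over the 16–20 weeks of waiting. The article sets it out as a formal superiority hypothesis with a sample size, inside a trial labelled randomised with three groups. It states no limit on how the result may be read. A reader of the eventual results could take 1b as randomised evidence of efficacy, which the described allocation would not support.

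The waiters are also treated later, so the same women could count as controls and as treated unless the analysis says otherwise.

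**Working it through.** **Step 1. Which contrasts are randomised.**
- CBT versus PED-t at first entry: allocated from the concealed list (Randomization). Randomised.
- CBT versus PED-t among former waiters: allocated at random after the wait (Methods and design). Randomised.
- Either treatment versus wait-list: the Abstract says surplus participants wait, Methods and design says the control group is those who have to wait, and the Randomization section limits the list to the two treatment arms. The three places agree, and none describes a chance mechanism for waiting. Not randomised as described.

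**Step 2. The plan's own figure for 1b.** The inputs, all from Statistical power and analyses, are a difference of 1.30 − 0.30 = 1.00 SD, covariate R² = 25%, alpha 0.05 (sidedness not stated) and power 0.80. The residual SD is √(1 − 0.25) = 0.866.
- Two-sided with the covariate: n = 2(1.960 + 0.842)² × 0.75 / 1.00² = 11.8, so 12 per group; 13 by noncentral t.
- One-sided without the covariate: n = 2(1.645 + 0.842)² / 1.00² = 12.4, so 13 per group; 14 by noncentral t.
- The other combinations give 10–11 (one-sided with covariate) and 16–17 (two-sided without).

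The stated 14 therefore reproduces to within two patients under the first two readings. Power at 14 per group, two-sided with the covariate: 1.00 / (0.866 × √(2/14)) = 3.06; 3.06 − 1.96 = 1.10; power 0.86. The sample size is not the problem.

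**Step 3. What a non-random control could do to the test.** This is an illustration; the prognostic difference is assumed and no value for it stands in the document. Let the treatments have no effect, and let waiters differ prognostically by b SD of the outcome after whatever the covariates remove. The noncentrality is b divided by the standard error, and the two-sided 5% test then rejects with the probabilities below.
- 14 versus 14: standard error 0.866 × √(2/14) = 0.327, 25 degrees of freedom.
- 72 versus 14 (one full treatment arm against the wait-list): standard error 0.866 × √(1/72 + 1/14) = 0.253, 83 degrees of freedom.

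| b (SD, assumed) | 14 vs 14 | 72 vs 14 |
|---|---|---|
| 0 | 0.05 | 0.05 |
| 0.1 | 0.06 | 0.07 |
| 0.2 | 0.09 | 0.12 |
| 0.3 | 0.14 | 0.22 |
| 0.5 | 0.31 | 0.50 |

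The larger comparison rejects more often, because added precision sharpens the test around a biased difference. The bias could equally run the other way and hide a real effect.

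**Step 4. Later entry into treatment.** This step is itself randomised, so it does not make 1b non-randomised and does not disturb PED-t versus CBT. It leaves two matters that the article does not settle: whether a waiter's treated phase also enters the treated side of 1b, and which assessment is her pre-treatment value. All outcomes are said to be measured five times (pre, post, 6, 12 and 24 months), and testing 1b needs a measurement at the end of the wait.

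**The case against.** The strongest reply is that the article discloses its design. The sentence that announces three groups also says what is randomised and who waits, and nowhere does the text claim that the wait-list was randomised. That is fair: the fault is a loose label plus a hypothesis presented without its limitation. Disclosure does not make the contrast randomised, however. Figure 2 (recruitment, screening and randomisation) is not available here and might add detail, but nothing in the text suggests a random draw.

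Several stronger readings are tempting and are not supported.
- *The main result is compromised.* It is not. Women are randomised between PED-t and CBT at both entry points.
- *Recruitment came in bursts, so waiters differ by route of entry.* The Recruitment section lists channels and gives no timing. Calendar-time differences are plausible; differences by route are conjecture.
- *Waiters keep their pre-wait baseline, so the expected untreated change of 0.30 is credited to treatment* (0.30/1.30 = 23% of the planned CBT effect). No section says this. Baseline measures precede randomisation, and waiters are randomised after the wait, which fits a fresh baseline. Even on the adverse assumption, with 14 waiters among 144, the average inflation would be 14/144 × 0.30 ≈ 0.03 SD, with no expected effect on PED-t versus CBT.
- *A baseline imbalance of 0.2–0.3 SD would bias 1b by the same amount.* If the covariate with R² = 25% is baseline severity (an assumption), the correlation is 0.5, so the unadjusted carry-over is 0.10–0.15 SD, and the planned ANCOVA is designed to remove it. What remains is unmeasured prognosis.
- *The non-inferiority claim rests on 1b.* The article does not say so; it takes the CBT effect and the margin from cited sources.

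The planned multilevel models also allow for repeated data within a woman. That deals with dependence, but not with how the control group was selected.

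**Conclusion.** The concern holds for hypothesis 1b alone. As described, the wait-list is an overflow group, and treatment versus wait-list is a non-randomised comparison inside a trial labelled randomised with three groups. Selection and calendar-time differences can bias it by an amount that the document does not allow one to bound. The rejection rates in the illustration (9% to 14% at 14 per group for an assumed 0.2–0.3 SD) show how such a bias would act; they do not estimate it. No stated number changes, and PED-t versus CBT is unaffected. This should be fixed, because it changes what the trial can claim about benefit over no treatment, but it does not threaten the main result.

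**What to change.** 1. For any oversubscribed intake still open, decide who waits by a concealed random draw. This needs a revised list with a wait-list allocation and a stated ratio, since the present blocks of eight cover two arms only. The later randomisation of waiters to CBT or PED-t can stay as it is.
2. For women already allocated by overflow, describe 1b as a non-randomised comparison wherever it is stated or reported, and adjust for baseline EDE-q, diagnosis and intake period.
3. Compare the waiting phase only with women treated immediately, so that no woman counts on both sides of 1b.
4. State that the end-of-wait assessment, which 1b already needs, is the pre-treatment baseline for waiters later treated.

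Items 2 to 4 are wording and analysis rules and remain possible if recruitment has closed. They call for no additional participants, and no extra visit as long as the end-of-wait assessment is made. The price is a more modest claim for 1b and, where intake continues, a small change to the allocation list. Adjustment reduces bias from measured differences only, so the limitation should be reported even after it is made.
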